# The group-based social skills training SOSTA-FRA in children and adolescents with high functioning autism spectrum disorder - study protocol of the randomised, multi-centre controlled SOSTA - net trial

**DOI:** 10.1186/1745-6215-14-6

**Published:** 2013-01-07

**Keywords:** Social skills training, Neural function, Moderating factors, Autism spectrum disorder

## Abstract

**Background:**

Group-based social skills training (SST) has repeatedly been recommended as treatment of choice in high-functioning autism spectrum disorder (HFASD). To date, no sufficiently powered randomised controlled trial has been performed to establish efficacy and safety of SST in children and adolescents with HFASD. In this randomised, multi-centre, controlled trial with 220 children and adolescents with HFASD it is hypothesized, that add-on group-based SST using the 12 weeks manualised SOSTA–FRA program will result in improved social responsiveness (measured by the parent rated social responsiveness scale, SRS) compared to treatment as usual (TAU). It is further expected, that parent and self reported anxiety and depressive symptoms will decline and pro-social behaviour will increase in the treatment group. A neurophysiological study in the Frankfurt HFASD subgroup will be performed pre- and post treatment to assess changes in neural function induced by SST versus TAU.

**Methods/design:**

The SOSTA – net trial is designed as a prospective, randomised, multi-centre, controlled trial with two parallel groups. The primary outcome is change in SRS score directly after the intervention and at 3 months follow-up. Several secondary outcome measures are also obtained. The target sample consists of 220 individuals with ASD, included at the six study centres.

**Discussion:**

This study is currently one of the largest trials on SST in children and adolescents with HFASD worldwide. Compared to recent randomised controlled studies, our study shows several advantages with regard to in- and exclusion criteria, study methods, and the therapeutic approach chosen, which can be easily implemented in non-university-based clinical settings.

**Trial registration:**

ISRCTN94863788 – SOSTA – net: Group-based social skills training in children and adolescents with high functioning autism spectrum disorder.

## Background

Autism spectrum disorders (ASD) are characterized by qualitative impairments in social interaction, reciprocal communication, and by stereotyped, repetitive behaviours. ASD comprise International Classification of Diseases, version 10 (ICD-10) diagnoses autism (F84.0), Asperger syndrome (F84.5), and atypical autism (F84.1), respective Diagnostic and Statistical Manual of Mental Disorders IV, text revision (DSM-IV TR) diagnoses autism (299.00), Asperger’s disorder (299.80) and pervasive developmental disorder-not otherwise specified (PDD-nos) (299.80). Recent epidemiological studies estimated a prevalence > 1% for all ASD, with about 45% showing an intelligence quotient (IQ) > 70 [1,2]. The rate of comorbid psychiatric disorders, especially attention-deficit/hyperactivity disorder (ADHD), anxiety and depressive disorders is high [3,4].

The treatment of choice in verbal school-aged children and adolescents with ASD and language and cognitive abilities in the average range, referred to as high functioning ASD (HFASD), is behaviour-based therapy to improve communication and social interaction with peers and adults. Group-based social skills training (SST) has been advocated as the most efficient treatment option. However, there is a scarcity of randomised controlled studies (RCT) implementing treatment manuals [5].

Review articles have delineated the following therapeutic goals that should be achieved by SST with ASD individuals [5,6]: increase of social motivation and social initiations, improvement of appropriate social responding, reduction of interfering behaviours and promotion of skill generalisation. Effective interventions are predominantly based on social learning theory, framing complex social conventions as rules that can be learned by, for example, modelling age-appropriate social interaction skills or teaching social scripts for common situations, and successively practising social interaction within the group by, for example, role play, video-modelling and direct feedback, as well as outside the group. In addition, operant methods as differential reinforcement of response attempts and positive behaviours are adopted. Some intervention methods also specifically aim at improving social understanding, emotion recognition, perspective-taking (that is, theory of mind abilities), and executive functions, as these aspects are specifically impaired in ASD [7]. As the aspect of generalisation, that is, the transfer and appropriate use of an acquired skill in other situations, is crucial for any effective SST program for children and adolescents with HFASD, generalisation sessions are added in several interventions. These can consist of community activities, training/interacting with typically developing peers, specific social interaction homework, or change of therapists during therapy [6].

Five RCTs in school-age children and adolescents with HFASD, including at least 10 children in the treatment group and implementing manualised training have been published to date [8-12]. A summary of the study characteristics, inclusion criteria and outcome measures are shown in Table 1. All studies were performed with children aged 7 to 12 years old; none included adolescent children. The studies differ considerably with respect to inclusion criteria, randomisation procedure (often not reported), kind and duration of the intervention, and outcome measures.

**Table 1 T1:** Characteristics of published randomised controlled trials on social skills training in high-functioning autism spectrum disorder (HFASD)

**Publication / comparison groups**	**Inclusion / exclusion criteria**	**Subjects, number; age; RP**	**Intervention**	**Manual**	**Outcome measures pre/post treatment**	**Results pre/post treatment**	**Effect size group x time #**
Beaumont and Sofronoff, 2008, Junior Detective Training Program / treatment versus wait-list control condition	Asperger syndrome; IQ > 85; no exclusion criteria reported	N = 49; 7.5-11 years; RP not described	4-weekly computer game training sessions (child and parents, 45 minutes) plus 8-weekly group therapy sessions with global targets (2 therapists / 3 children, 75 minutes); parallel 8-weekly parent trainings; teacher handouts	Yes	No primary outcome measure		
					SSQ-P (PR)	*P* < 0.001	η^2^ = 0.37
					ERSSQ-P (PR)	*P* < 0.001	
					Child measures:		
					Emotion recognition	ns	
					Knowledge of emotion management strategies	*P* < 0.001	
					Treatment effect was maintained for 5 months (parent ratings)		
DeRosier *et al*., 2011 S.S.GRIN-HFA / treatment versus traditional S.S.GRIN	Autism, Asperger syndrome, PDD-nos; IQ > 85; exclusion of children with CBCL-aggression subscale > 70	N = 55; 8-12 years; RP not described	S.S.GRIN-HFA: 15 group sessions of 60 minutes, and 4 parent training sessions; traditional S.S.GRIN: 10 group sessions of 60 minutes (2 therapists/group)	Yes	No primary outcome measure		
					Parent report: SRS – subscales	*P* < 0.05	d: 0.68 - 0.94
					ALQ	*P* < 0.05	d = 0.75
					Child report:		
					Social dissatisfaction		
					questionnaire	ns	
					Social self-efficacy scale	ns	
Frankel *et al*., 2010 Children’s Friendship Training” / treatment versus wait-list control condition	Autism spectrum disorder (ADI-R, ADOS); verbal IQ > 60; child has to be able to switch topics in conversation and knows several play rules; attending regular classroom without individual support; exclusion criteria: psychotropic medication; neurological or medical disorder	N = 76 randomised, n = 68 completed training (58 boys, 10 girls); 7 - 12 years; RP: random.org	12 weeks of CFT within classes conducted by the UCLA friendship program; 12 session of 60 minutes for the child; 12 parallel sessions of 60 minutes for parents parents support homework and generalisation (i.e. arranging play dates)	Yes	No primary outcome measure		
					Child report:		
					The loneliness scale	*P* < 0.025	
					Piers-Harris self-concept scale	*P* < 0.025	
					parent report:	2 subscales *P* < 0.001	
					QPQ-P (5 subscales)		
					SSRS (4 subscales)	1 subscale *P* < 0.05	
					Teacher report: PEI treatment effect was maintained for 3 months (parent ratings)	ns	
Koenig *et al*., 2010 / treatment versus wait-list control condition	Pervasive developmental disorder (ADOS, SCQ, PDD-BI) full scale IQ >= 70; exclusion criteria: severe aggressive behaviour, self-injury, oppositional behaviour	N = 44; 8-11 years (34 boys, 10 girls); RP: by external faculty member	16 group therapy sessions of 75 minutes (2 therapists / 4-5 children, 2 peer tutors); after 3^rd^ session: individual treatment plan for each child (pro-social behavioural objectives; strategies)	Yes	Primary outcome measure: CGI-I	*P* = 0.001	
					Secondary outcome measure: Prosocial Index of the Social Competence Inventory (PR)	ns	
Lopata *et al*., 2010 / treatment versus wait-list control condition	Autism, Asperger Syndrome, PDD-nos IQ > 70, verbal IQ > 80; no exclusion criteria reported	N = 36; 7-12 years; RP not described	Summer training program: 5 weeks with 5 × 70 minutes treatment cycles/day and 3 therapists/6 children; parents: 1/week parent training of 90 minutes	Yes	Set of primary outcome measures; child measures:	One-tailed tests	
					social skills knowledge	*P* < 0.001	d = 1.27
					DANVA-2	ns	d = 0.53
					CASL	*P* < 0.001	d = 0.39
					parent ratings:		
					ASC	*P* = 0.006	d = 0.58
					SRS	*P* = 0.003	d = 0.63
					BASC-2-PRS: withdrawal	*P* < 0.001	d = 1.06
					BASC-2-PRS: social skills	ns	d = 0.37

ADI-R, Autism Diagnostic Interview-revised; ADOS, Autism Diagnostic Observation Schedule; ALQ, Achieved Learning Questionnaire; ASC, Adapted Skillstreaming Checklist; BASC-2-PRS, Behavior Assessment System for Children, 2^nd^ edition, parent rating scales; CASL, Comprehensive Assessment of Spoken Language; CBCL, Child Behavior Checklist; CFT, Children’s Friendship Training; CGI-I, Clinical Global Impressions Scale Improvement Item; DANVA-2, Diagnostic Analysis of Nonverbal Accuracy 2; ERSSQ, Emotion Regulation and Social Skills Questionnaire; ns, not significant; PDD-nos, Pervasive Developmental Disorder-not otherwise specified; PDD-BI, Pervasive Developmental Disorders Behaviour Inventory; PEI, The Pupil Evaluation Inventory; PR, parent report; QPQ, Quality of Play Questionnaire; RP, randomisation procedure; SCQ, Social Communication Questionnaire; SRS, Social Responsiveness Scale; SSQ-P, Social Skills Questionnaire, parent version; SSQ-T, Social Skills Questionnaire, teacher version; SSRS, Social skills rating system; TPSS, Teacher Perception of Social Skills.

# Effect sizes are shown were reported.

One study implemented a very intensive summer treatment programme over 5 weeks [12], and one was based within school settings [10]. One study aimed at targeting individual child-specific aims within a group-based setting [11]. The two remaining studies used the classical format of highly structured social skills training with weekly sessions for the children and additional parent training sessions of varying intensity [8,9].

With respect to inclusion criteria, both latter studies only included children with IQ > 85, whereas the other studies also included less cognitively able children with IQ > 60 or IQ > 70. Most studies did not report specific inclusion or exclusion criteria apart from the diagnosis of ASD, which, however, was not specifically confirmed by a standardised assessment prior to start of therapy in all studies. As ASD are heterogeneous disorders with a high rate of psychiatric and medical comorbidity and a variable course, not reporting standardised diagnostic assessment of ASD before start of the intervention, and not reporting psychiatric respective medical comorbid disorders are strong limitations of the published studies. In addition, only one study mentioned the use of psychotropic medication as an exclusion criterion [10], whereas the other studies did not report any information on the use of psychotropic medication. As the additional use of psychotropic medication is a major possible confounding factor, this is another limitation of most studies.

With respect to outcome measures, all studies implemented different parent rating scales for assessing social skills, which showed a positive effect of the respective training in all studies. Most studies did not report a primary outcome measure, but used several outcomes simultaneously. Effect sizes were not reported in all studies, and the long-term effect after 3 or 5 months of therapy was only assessed in two studies [8,10]. Where reported, effect sizes differed strongly by outcome measure between small and large effects. A few studies implemented child-based measures, which showed less strong or no effects compared to parent ratings.

Taken together, the previous randomised controlled studies on social skills training showed a medium to large effect on parent-reported social skills in children with ASD directly after the end of therapy, but suffer from several methodological and practical limitations. Thus, the present SOSTA-net trial aimed at overcoming several of these limitations by defining clear inclusion and exclusion criteria, one primary outcome and several secondary outcome measures assessing immediate and long-term effects of the therapy after 3 months, using a specific randomisation procedure, and also including adolescents and young adults in the trial. In addition, the large sample size (see below) will also allow the study of factors influencing therapy outcome, which is strongly relevant for clinical practice.

The first German group-based social skills training was developed at the Department of Child and Adolescent Psychiatry at JW Goethe University Hospital, Frankfurt am Main. A pre-post pilot study showed good acceptance of the intervention in individuals with HFASD and their parents, and was effective in improving social interaction with adults and peers [13]. As this first SST was designed as ongoing group training, and therefore did not contain a detailed manual for a limited number of group therapy sessions, in the current RCT, the effect of 12 sessions of a revised version, the manualised SOSTA-FRA programme is compared to treatment as usual (TAU), including wait-list, control condition. It is hypothesized that social responsiveness in children and adolescents with HFASD will improve more strongly with the group-based SOSTA-FRA training than by the TAU/wait-list.

As the effects of the previous SST studies varied across and within groups, it also is relevant to explore factors associated with treatment outcome. Well-established positive predictive factors are IQ and language ability. Less well-established influencing factors are severity of autistic symptoms in the three core domains; age, gender, psychiatric comorbid disorders, genetic risk factors, and medication effects [5,13,14]. These will be assessed in an exploratory fashion in the present study. In addition, the effect of SST on underlying brain mechanisms is examined by the electroencephalographic response to implicit and explicit facial emotion and biological motion recognition as correlates of social brain function.

## Methods/design

The SOSTA-net trial is designed as a prospective, randomised, controlled, multicentre trial, including an intervention and a waiting-list control group. The intervention includes 12 highly structured, manualised (SOSTA-FRA manual), weekly group-based social skills training, each of 90 minutes duration. Five children or adolescents take part in the intervention group, and the number of skilled behavioural therapists (that is, those who have studied at university for a minimum of 5 years and have undergone > 2 years of additional psychotherapy training) in each group is two (child-therapist ratio = 5:2). In addition, three parent training sessions are scheduled at the beginning, middle and end of the group therapy sessions, both for the intervention and the control group. The wait-list control group receives the same social skills training after the end of trial, that is, after 6 months (3 months intervention and 3 months follow-up).

### Objectives and hypothesis

It is hypothesized that add-on group-based SST using the manualised treatment program SOSTA-FRA will result in improved social responsiveness and pro-social behaviour compared to TAU. The parent-rated Social Responsiveness Scale (SRS), obtained at baseline, directly after intervention, and at 3 months follow-up is the primary outcome measure of interest (see below).

Several additional aspects with regard to secondary outcome measures will be studied: A second scale, the Strength and Difficulties Questionnaire (SDQ), assessing pro-social behaviour, total and peer-related problems, will be obtained from parents, and improvements in all three areas are expected. Also, it is expected, that social responsiveness (SRS), pro-social behaviour, total and peer-related problems (SDQ) as reported by teachers will be improved. These are measures of generalisation of the acquired social skills into the classroom. In addition, a positive effect on parent- and self-rated anxious and depressive symptoms is expected.

Variables that could possibly moderate treatment effect, including age, IQ, sex, comorbid disorders, ASD symptom severity, medication and common variants of genes related to social interaction will be explored. Exclusively in Frankfurt, changes in neural function during perception of social stimuli, measured by electroencephalograpy (EEG), will also be assessed pre- and post-therapy and at 3 months follow-up.

### Study centres

The trial is performed by close cooperation between six University Hospital Departments of Child and Adolescent Psychiatry, Psychosomatics and Psychotherapy in Germany, which provide a special outpatient service for individuals with ASD: Aachen, Frankfurt/Main, Homburg/Saar, Köln, Wuerzburg, and Mannheim. Data management, biometric support and statistical analyses are provided by the Institute of Medical Biometry and Informatics (IMBI), University of Heidelberg. Study monitoring is done by the Coordination Centre for Clinical Trials (KKS), University of Heidelberg.

### Participants‘ inclusion and exclusion criteria

A diagnosis of autism, Asperger syndrome or atypical autism (ICD-10) is essential to be included in the study. Diagnostic assessment is standardized according to ICD-10, by obtaining a detailed medical history, performing the Autism Diagnostic Interview-Revised (ADI-R), the Autism Diagnostic Observation Schedule (ADOS), and a standardized intelligence testing (HAWIK-IV, WIE). Patients’ incusion and exclusion criteria are listed in Table 2. Comorbid psychiatric disorders are diagnosed according to ICD-10 and DSM-IV TR by a German validated structured interview on psychiatric disorders in children, the Diagnostic interview on psychiatric disorders in children, German version (Kinder-DIPS) [15]. The sample comprises a group of children and adolescents with high-functioning autism, Asperger Syndrome, and atypical autism who are typical participants of SST in ASD. Inclusion and exclusion criteria with regard to other psychiatric disorders are broad, by only excluding individuals with schizophrenia, bipolar disorder, social phobia, obsessive-compulsive disorder, major depressive disorder with suicidal ideation, or any personality disorder as well as aggressive behaviour interfering with group therapy. This approach reflects the high rate of comorbid psychiatric disorders in ASD [4], which are likely to be relevant with respect to therapeutic outcome. Only disorders which require a more specific and different kind of psychopharmacotherapy and/or psychotherapy were excluded as comorbid disorders. Other frequent comorbid disorders, such as attention-deficit/hyperactivity disorder or oppositional behaviour as well as specific phobias or depressive episodes without suicidal ideation, were no reason for exclusion. They will be assessed in secondary analyses as possible moderating factors of therapy outcome. Similarly, inclusion criteria with regard to cognitive abilities were rather broad allowing children with IQ >=70 into the study. We will enrol 220 subjects into the clinical trial, that is, 110 subjects per treatment group. Only a single participation in the trial is allowed.

**Table 2 T2:** Inclusion and exclusion criteria of the SOSTA-net trial

**Inclusion criteria**	Diagnosis of autism spectrum disorder (ICD-10: F84.0, F84.5, F84.1)
	Age 8-20 years at start of group therapy
	Informed consent
	No, or stable psychopharmacotherapy
	Children and parents are fluent in reading German to be able to understand instructions and fill in questionnaires
**Exclusion criteria**	IQ < 70 (full scale IQ according to HAWIK-IV/WIE)
	Psychiatric disorders: schizophrenia, bipolar disorder, social phobia, obsessive-compulsive disorder, major depressive episode with suicidal ideation, any personality disorder
	Aggressive behaviour interfering with group therapy
	Any neurological disorder (exception: well treated epilepsy)
	Other medical condition interfering with therapy
	Group-based SST during last 6 months prior to the study
	Participation in other clinical trials including observation period of competing trials

HAWIK-IV/WIE, Wechsler Scales for children, adolescents and adults with current German norms, measuring IQ; IQ, intelligence quotient.

### Criteria for withdrawal

Subjects can withdraw from the trial (1) at their own request or at the request of the legal representative; (2) if in the investigator’s opinion continuation of the trial would be detrimental to the subject’s well-being; (3) on admission to a psychiatric clinic; (4) if in the investigator’s opinion the realisation of the program is no longer possible due to the patient’s behaviour in group therapy sessions, for example, oppositional or aggressive behaviour directed against other group members or herself/himself. A change in pharmacotherapy is not a criterion for withdrawal from the trial.

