### Assessment

The trial time flow is shown in Figure 1. After verifying the diagnosis of HFASD and screening for eligibility (T1), ten individuals are included in an age-homogenous study group. The participants are then randomised to the intervention and control group, and the baseline assessment (T2) takes place. Following randomisation, the first parent training (both for parents of the children in the intervention and the control group) and the first SST group session of at least five individuals are performed. Mid-intervention assessment takes place after 6 weeks group training, parallel with the second parent training. This mid-intervention assessment (T3) aims at obtaining the primary and secondary outcome measures during the ongoing trial to get some information on individuals dropping out from the study before T4. One week after the last group SST session, the third parent training is provided and post assessment takes place (T4). To assess the stability of the therapy effects, the study also includes a follow-up (T5) measurement 3 months after finishing the SST.

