### Statistical analysis

Confirmatory analysis is performed for the ITT population, and is defined on the basis of the ITT principle. An additional per-protocol analysis will be conducted, which will include all patients without major protocol violations. Two primary endpoints are assessed in confirmatory analysis, namely the change in SRS total score between baseline and 12 weeks after baseline (effect at the end of therapy) and the change in SRS total score between baseline and three months after the end of therapy (maintenance effect). To ensure control of the multiple type I error rate at 5%, a hierarchical test procedure will be applied [23]: The first null hypothesis to be tested states that the change in SRS total score between baseline and 12 weeks after baseline is equal for both groups. If this hypothesis can be rejected at the two-sided significance level of 5%, the second null hypothesis stating that the change in SRS total score between baseline and three months after the intervention is equal in both groups is tested at the two-sided level 5%. If the first null hypothesis cannot be rejected, the second null hypothesis referring to the co-primary endpoint is also accepted.

Both null hypotheses will be tested by analysis of covariance with the covariates baseline SRS total score, age, IQ, and centre. Gender and medication effects were not observed in previous studies [14], and hence these variables are not included in the model of the primary analysis. Missing values with respect to post-baseline primary outcomes will be handled by application of the mixed-effects model for repeated measures (MMRM) approach that turned out to show favourable characteristics in terms of the type I error rate, power, and bias of estimates as compared to alternative methods dealing with missing values, such as last-observation-carried-forward (LOCF) [24-26].

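### Withdrawal criterion (4) lets only the intervention arm lose T4 and T5 outcomes, because disruptive behaviour in sessions is a ground for leaving the trial and not just the group

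*Protocol article*

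**What the plan says.** The section Criteria for withdrawal opens with "Subjects can withdraw from the trial (1) at their own request" and lists four grounds. The fourth is that the investigator considers the programme no longer feasible because of the patient's "behaviour in group therapy sessions, for example, oppositional or aggressive behaviour directed against other group members or herself/himself". The section closes by saying that a change of medication is not such a ground, again with reference to the trial and not the sessions.

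Other sections bear on this:

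- Methods/design, on the control arm: "The wait-list control group receives the same social skills training after the end of trial, that is, after 6 months".
- Participants' inclusion and exclusion criteria, on comorbidity: "attention-deficit/hyperactivity disorder or oppositional behaviour as well as specific phobias or depressive episodes without suicidal ideation, were no reason for exclusion". Table 2 does exclude aggressive behaviour that would interfere with group therapy.
- Assessment, on why SRS and the other outcomes are also taken at T3: "to get some information on individuals dropping out from the study before T4".
- Statistical analysis: "Confirmatory analysis is performed for the ITT population, and is defined on the basis of the ITT principle", and "Missing values with respect to post-baseline primary outcomes will be handled by application of the mixed-effects model for repeated measures (MMRM) approach". LOCF is named as an example of an alternative imputation for sensitivity analysis, alongside a per-protocol analysis.

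**The concern.** Criterion (4) ties leaving the trial to an event that can occur only in one randomised arm. The judgement is made after randomisation by someone who must know the allocation, since it concerns conduct in the sessions. It is also plausibly related to outcome: the programme teaches self-regulation, impulse control and coping with anger, so a child removed for oppositional or aggressive conduct may be one who is not benefiting.

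An ITT comparison needs T4 and T5 outcomes from every randomised child as far as they can be obtained. If children who leave the group also leave the trial, the intervention arm may lose outcomes selectively with no matching loss among controls. MMRM then treats these children like retained children in the same arm with the same covariates and observed scores. If they in fact did worse than that, the effect of training is overstated.

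**Working it through.** **1. Can a control child meet criterion (4)?** It requires conduct in group sessions. Control children receive their training only after the six-month trial period, which ends with T5. So they cannot meet it while under observation. Criteria (1) to (3), namely own request, detriment to well-being and psychiatric admission, can apply in either arm.

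**2. Does the plan separate leaving the sessions from leaving the trial?** Not in the article. The wording is withdrawal from the trial. T3 is partly justified by people who drop out before T4, and the sample size section counts dropouts as not evaluable. These point towards an end of follow-up, but none states it.

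**3. The plan's own figures.** Inputs from Sample size calculation: difference 11, SD 28, two-sided 5%, power 80%. The two-sample t-test (noncentral t) gives 80.1% power at 103 per arm and 79.7% at 102, so 2 × 103 = 206 is reproduced. With 5% dropout, 206 / 0.95 = 216.8, or 217; randomising 220 leaves 220 × 0.95 = 209. The sample size is not affected by this point.

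**4. Size of a possible bias.** Let f be the share of the intervention arm removed under criterion (4), and D the amount by which their mean SRS change is worse than MMRM predicts from their observed data.

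Bias = f × D.

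Neither f nor D is in the document; both are assumptions. For scale, D = 11 is a child who makes no gain where the model predicts the planned 11, and D = 28 is one full SD. With 110 children in the arm, f = 2%, 5% and 10% are about 2, 5 to 6, and 11 children. In groups of five there are 110 / 5 = 22 groups, so 10% is one removal in every second group.

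For the type I error, SE = 28 × √(2/103) = 3.90, and the two-sided rejection rate is Φ(−1.96 + bias/SE) + Φ(−1.96 − bias/SE).

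| f | D | Bias (points) | Share of 11 | Type I error |
|---|---|---|---|---|
| 2% | 11 | 0.22 | 2% | 5.0% |
| 2% | 28 | 0.56 | 5% | 5.2% |
| 5% | 11 | 0.55 | 5% | 5.2% |
| 5% | 28 | 1.40 | 13% | 6.5% |
| 10% | 11 | 1.10 | 10% | 5.9% |
| 10% | 28 | 2.80 | 25% | 11.1% |

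The plan's 5% is dropout for all reasons, so f = 5% already assigns the whole planned dropout in that arm to criterion (4).

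**5. Do the planned methods cover it?** MMRM is valid if data are missing at random given what was observed. A child removed after T3 has a mid-intervention score that helps, provided T3 is among the modelled visits. A child removed before T3 has no post-baseline SRS at all. For that child LOCF assigns no change, which can represent failure to improve but not worsening. Neither LOCF nor the per-protocol analysis is aimed at informative loss in one arm only.

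**The case against.** The strongest reply is that the text is permissive ("Subjects can withdraw from the trial") and never says that questionnaires stop. The article condenses a fuller protocol, where data collection after withdrawal would normally be set out. T3 may be meant for families who leave at their own request, from whom later data cannot be required. This stands: an end to T4 and T5 follow-up is an inference. What remains is that the article states a rule, in terms of the trial, that one arm alone can trigger.

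Several stronger readings are tempting and are not supported:

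- *The children are dropped from the ITT analysis.* Nothing says so. They stay in the population, and the issue is missing outcomes.
- *The comparison is biased towards training.* The endpoint is caretaker-rated SRS change adjusted for baseline SRS, age, IQ and centre, not conduct in the group. No passage links the two after adjustment. The entry exclusion for aggressive behaviour should also make such removals less common.
- *Psychiatric admission is a one-sided loss too.* Criterion (3) applies to both arms, and admissions among controls could act in the opposite direction.
- *Adverse event follow-up is cut short.* Safety aspects covers events during and up to three months after treatment and makes no exception for withdrawn children.

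**Conclusion.** The point holds for criterion (4) only. As written, it permits loss of T4 and T5 outcomes confined to the intervention arm, through an unblinded judgement after randomisation that may be related to response. This sits badly with a confirmatory ITT analysis, and the named missing-data methods do not address it fully.

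The direction of any bias is plausible but not demonstrated, and its size rests wholly on assumed values of f and D. At 2% to 5% removal it is about 0.2 to 1.4 points against the planned 11, with type I error between 5.0% and 6.5%. The combination that would matter most is about 10% removal with a large deficit that MMRM does not recover. This is worth correcting because the correction is cheap; it does not by itself put the primary analysis in doubt.

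**What to change.** Restate criterion (4) as a reason for ending participation in the group sessions, not in the trial. The clinical decision on when a child leaves a group stays exactly as it is, and criteria (1) and (2) are left alone.

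State that children who leave the sessions this way, and where feasible those admitted to a psychiatric clinic, continue the T3 to T5 caretaker questionnaires and adverse event collection unless consent for data is withdrawn. Use those scores in the ITT analysis. Report reasons for leaving, and their timing relative to T3, by arm.

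The cost is amendment wording and a small tracing effort. The primary outcome is a caretaker questionnaire, so the child need not attend sessions to supply it. As 204 patients had been randomised by October 2012, the amendment mainly helps those still in follow-up; the reporting of reasons by arm can cover everyone.
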